## Abstract

**Background:**

Intramuscular vitamin A supplementation decreases the risk of bronchopulmonary dysplasia (BPD) in very-low-birth-weight preterm infants without significant adverse effects. However, intramuscular vitamin A supplementation is not widely accepted because of the discomfort and risk of trauma associated with repeated injections. Enteral vitamin A supplementation has not been studied adequately in the clinical trials. Enterally administered water-soluble vitamin A is absorbed better than the fat-soluble form. We hypothesised that enteral administration of a water-soluble vitamin A preparation will decrease severity of BPD compared with a control group receiving placebo.

**Methods:**

We plan a double-blind randomised placebo-controlled trial at a tertiary neonatal-perinatal intensive care unit. Eligibility criteria include infants born at less than 28 weeks’ gestational age and less than 72 h of life. Infants with major congenital gastrointestinal or respiratory tract abnormalities will be excluded. After parental consent, infants will be randomized to receive either enteral water-soluble vitamin A (5000 IU once a day) or placebo. The intervention will be started within 24 h of introduction of feeds and continued until 34 weeks’ post-menstrual age (PMA).

The primary outcome is severity of BPD at 36 weeks’ PMA. Severity of BPD will be assessed objectively from the right-shift of the peripheral oxyhaemoglobin saturation versus partial pressure of inspired oxygen (SpO_2_-PiO_2_) curve. We require 188 infants for 80% power and 5% significance level based on an expected 20% decrease in the right shift of the SpO_2_-PiO_2_ curve in the vitamin A group (primary outcome) compared with control group at 36 weeks’ PMA, and a 20% attrition rate.

Secondary outcomes will be plasma and salivary concentrations of vitamin A on day 28 of the trial (first 30 infants), lung and diaphragm function, clinical outcomes at 36 week’ PMA or before discharge/death, and safety of vitamin A.

**Discussion:**

BPD poses a significant economic burden on the health-care system. If our study shows that enteral supplementation of water-soluble vitamin A is safe and effective for decreasing the severity of BPD, it will provide the opportunity to further evaluate a simple, globally acceptable preventive therapy for BPD.

**Trial registration:**

ANZCTR; ACTRN12616000408482 (30th March 2016).

**Electronic supplementary material:**

The online version of this article (10.1186/s12887-017-0958-x) contains supplementary material, which is available to authorized users.

## Background

Bronchopulmonary dysplasia (BPD) is a major respiratory morbidity associated with premature birth and affects 41% of the infants born before 28 weeks of gestational age [1]. BPD is associated with significant long-term health-consequences, which may persist to school age and adolescence. Infants with BPD are more likely to have chronic cough and asthma like symptoms in school age, abnormal lung function and lung imaging in adolescence, and greater need for hospitalisation and respiratory morbidity as compared with premature infants of similar gestational age without BPD [2–4]. Even more importantly, BPD may adversely influence long-term neurodevelopmental outcomes [5–7]. The current armamentarium for prevention of BPD includes surfactant, caffeine, lung protective ventilation strategies, and targeted oxygen saturation. BPD remains a heavy burden on healthcare resources despite current integrated approaches to therapy for BPD.

Low plasma and tissue concentrations of vitamin A in very low birthweight (VLBW) infants may contribute to the pathophysiology of BPD [8]. Intramuscular (IM) vitamin A supplementation decreases the incidence of BPD in VLBW infants [9, 10]. However, the practice of IM vitamin A supplementation is not widely accepted because of the discomfort and risk of trauma associated with repeated IM injections [11]. In addition, high cost and limited availability of Vitamin A parenteral preparations may further deter physicians from the use of IM vitamin A for prevention of BPD [12]. The intravenous (IV) route of administration is invasive, difficult to maintain for a long term, and associated with increased risk of infection: hence IV administration of Vitamin A is not suitable for prolonged duration of preventive therapy in preterm infants.

Enteral administration of Vitamin A offers a less-invasive route of administration; however, enteral Vitamin A is not well evaluated in the preterm infant. Two randomised controlled trials (RCT) by Wardle et al. and Calisici et al. did not show a significant beneficial effect of enteral vitamin A supplementation for prevention of BPD [13, 14]. The ineffectiveness of enteral vitamin A supplementation for prevention of BPD may be related to decreased bioavailability of enteral vitamin A in the preterm infant. Nevertheless, the RCT by Calisici et al. was only presented as an abstract and hence provides inadequate details about intervention and outcomes. Similarly, the trial by Wardle et al. was limited by inadequate sample size for the primary outcome of BPD, use of postnatal steroids in a large proportion of the study infants, and use of a low vitamin A dose in infants that were at highest risk of BPD [13, 14].

The exact mechanisms involved in the process of absorption of vitamin A through the gut are unclear. Poor absorption of enteral vitamin A in extremely preterm infants may be related to decreased hydrolysis of retinyl esters, decreased availability of bile salts required for formation of micelles, or inadequate availability of carrier proteins required for absorption of vitamin A in enterocytes [15]. Passive diffusion is the predominant mode of absorption at high intraluminal concentrations of vitamin A [16]. In contrast, protein-mediated transport predominates at lower intraluminal concentrations of vitamin A [16]. The small particle size of Vitamin A in the water-soluble form may be advantageous for improved absorbance by diffusion as compared to the larger particle size of the fat-soluble Vitamin A preparations. The water-soluble form of vitamin A is absorbed better by preterm infants compared with the fat-soluble form [17]. The water versus fat-solubility of vitamin A preparations may be critical to interpretation of randomised trials of enteral vitamin A: Wardle et al. and Calicisi et al. did not report the form of vitamin A used in their RCTs [13, 14]. The NeoVitaA trial is using a fat-soluble form of vitamin A ([18] and personal communication). To our knowledge there are no RCTs investigating enteral supplementation of a water-soluble form of vitamin A for prevention of BPD.

Our objective is to undertake a randomised controlled trial to determine if extremely preterm infants (< 28 w gestation) receiving enteral water soluble Vitamin A supplements from commencement of enteral feeds until 34 w PMA compared to a placebo enteral supplement, will have a reduced severity of BPD at 36 w PMA (Additional file 1). We hypothesize that compared to placebo, enteral supplementation with water-soluble vitamin A will decrease the severity of BPD as measured by right shift in the peripheral oxyhaemoglobin saturation versus partial pressure of inspired oxygen (SpO_2_-PiO_2_) curve [19]. We will define a clinically significant reduction in BPD severity as a 20% decrease in the right shift of the SpO_2_-P_i_O_2_ curve: this change approximates the shift required to change from severe BPD to moderate BPD, moderate BPD to mild BPD, or mild BPD to no BPD (unpublished observations, [name]).

A sub-study will evaluate the utility of salivary retinol for assessment of Vitamin A status (Vitamin A plasma-saliva correlation sub-study). Use of saliva for the measurement of hormones and vitamins is gaining attention because of its ease of collection, painless nature and low potential for patient harm. Adult salivary and plasma retinol are correlated strongly [20]. A strong correlation of salivary and plasma retinol in very preterm infants will facilitate development of acceptable and non-invasive assessment of vitamin A status in these infants.

## Methods

### Study design and setting

A placebo-controlled double-blind randomised trial (RCT) in a tertiary neonatal intensive care unit. The study schedule is shown in Fig. 1.

**Fig. 1 Fig1:**
[figure not shown]
EVARO study schedule. PMA: Post menstrual age

Inclusion criteria:Infants born at less than 28 weeks’ gestational age.Less than 72 h after birth.Informed and signed consent from the parents or legal guardian

### Exclusion criteria

Infants with major congenital gastrointestinal or respiratory tracts abnormalities will not be recruited.

Infants admitted in the neonatal intensive care unit will be screened for the eligibility by the chief investigator (AR). AR will approach the parents/legal guardian of the infants and obtain informed consent for the participation in the study.

### Primary outcome

Right shift of SpO_2_-PiO_2_ curve indicates impaired gas exchange and correlates with the severity of BPD using the NICHD classification of BPD severity [19]. The right shift of the SpO_2_-PiO_2_ curve will be assessed at 36 weeks’ (range 35 to 37 week) PMA.

Our decision to use right shift in SpO_2_-PiO_2_ curve as the primary outcome rather than the NICHD categorical classification based on requirement for supplemental oxygen and/or mechanical respiratory support at 36 weeks’ PMA (current clinical BPD severity discriminator) [21] is due to limitations of the NICHD definition: the categorical severity descriptors have limited discriminatory capacity; the SpO_2_ criteria used to prescribe oxygen supplementation vary between clinical units; and the SpO_2_ for any given fractional inspired oxygen (FiO_2_) is affected by altitude of the test site, making it difficult to compare results of two places at different altitude. Reduced alveolar ventilation:perfusion (V_A_/Q) ratio (as assessed using SpO_2_-PiO_2_ curve) is the predominant mechanism of impaired gas exchange in BPD. V_A_/Q ratio can be quantified non-invasively and provides an objective continuous measure of BPD severity, regardless of altitude. Improvement in the V_A_/Q ratio reflects decreased severity of BPD and is detected by decreased right shift of SpO_2_-PiO_2_ curve. Further, the SpO_2_-PiO_2_ curve differentiates oxygen requirement resulting from V_A_/Q mismatch from right-to-left shunt because V_A_/Q mismatch displaces the entire curve to the right while right-to-left shunt lowers the plateau of the curve [19].

#### Measurement of SpO_2_-PiO_2_ curve [22, 23]

BPD severity will be determined at 36 weeks’ PMA or before transfer/discharge if transfer/discharge occurs before 36 weeks’ PMA. The infant’s baseline SpO_2_ will be recorded at the prevailing PiO_2_. PiO_2_ will be incremented or decremented by ~ 2 kPa at 5 min intervals until at least five SpO_2_ measures in the range of 86-97% are recorded (lowest permissible PiO_2_ 14 kPa). Paired measurements of SpO_2_-PiO_2_ are plotted, and the right-shift and V_A_/Q are determined using an algorithm described by Quine et al. [19].

**Secondary outcomes**:Plasma-saliva correlation sub-study (first 30 study infants): Paired saliva and blood samples will be collected to assess correlation between salivary and plasma retinol levels. Saliva (0.25 mL) will be collected using purpose-designed swabs (SalivaBio Infants Swab, Salimetrics™ USA). Paired samples of plasma and saliva will be stored at −80 °C until further analysis. Retinol concentration in the samples will be measured using high performance liquid chromatography with mass spectroscopy [24, 25].

A plasma retinol level > 0.70 μmol·L^−1^ is considered normal while levels of <0.35 μmol·L^−1^ and 0.35 – 0.7 μmol·L^−1^ are considered to be ‘deficient’ and ‘low’ respectively.2.Relative Dose-Response test (RDR) (30 study infants): During the initial phase of vitamin A deficiency, the plasma retinol concentration remains within normal range at the cost of liver vitamin A stores. The plasma retinol value correlates poorly with liver stores until plasma retinol becomes very low (< 0.35 μmol·dL^−1^). RDR reflects the vitamin A status of an individual better than plasma retinol. The RDR test is based on the principle that apo-retinal binding protein (RBP) accumulates in the liver during vitamin A deficiency. A challenge dose of vitamin A allows retinol to bind to excess hepatic RBP, which is exported into the plasma as the holo-RBP-retinol complex, thereby increasing plasma retinol concentration. The proportional rise in the plasma retinol concentration correlates directly with the severity of liver vitamin A depletion. A RDR value of >20% indicates deficient liver vitamin A stores [26].

The RDR will be measured on day 28 of the trial, 24 h after the previous study dose. Baseline plasma retinol (B_0_) will be estimated from a blood sample (0.5 mL) collected in a lithium heparin tube (BD Microtainer™ Plasma Separator Tube). Capillary, venous or arterial samples are acceptable, as method of collection does not influence plasma retinol values significantly [27]. Whenever possible, the blood sampling will be performed along with the routine blood investigations to avoid additional skin pricks to the infant. The tube will be labelled and wrapped with aluminium foil to protect the sample from light. Plasma obtained by immediate centrifugation at 3000 rpm for 5 min will be stored at −80 °C until further analysis.

After collection of the B_0_ sample, 5000 IU vitamin A (open label) will be administered through a gastric tube to the infant. Five hours after the administration of vitamin A, a second blood (B_5_) sample will be collected and stored using the same technique employed for collection and storage of baseline samples. RDR will be calculated using the formula: Blood RDR = (B_5_ – B_0_) × 100/B_5_
3.Other secondary outcomes measured at discharge or death: Death before discharge; moderate to severe BPD [21]; use of postnatal steroids for BPD; duration of supplemental oxygen; proportion of infants discharged with home oxygen, days of mechanical ventilation; days of positive pressure support (mechanical ventilation + continuous positive airway pressure + humidified high flow); weight gain (gram/day) during the period of study medication supplementation; retinopathy of prematurity requiring treatment in the form of laser ablation or bevacizumab injection [28]; diagnosis of culture positive sepsis (blood or cerebrospinal fluid); diagnosis of suspected sepsis (C-reactive protein >25 mg·L^−1^ and treatment with antibiotics for at least 5 days); grade 3 or 4 intraventricular haemorrhage /periventricular leucomalacia [29]; stage 2a or greater necrotizing enterocolitis [30]; and vitamin A adverse effects.

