### Sample size

The normal SpO_2_:PiO_2_ curve in adults is shifted to the right of oxygen-haemoglobin dissociation curve by 6 kPa. Preterm infants with moderate to severe BPD have a mean (SD) shift of 16.5 (4.7) kPa [19]. We estimate that up to 20% of the recruited infants may not have SpO_2_-PiO_2_ measurement done at 36 weeks due to death, withdrawal of consent, and transfer of the patient to other hospitals. Allowing for this 20% loss of the cohort before measurement of the primary outcome, the required sample size is 188 (94 in each group) to detect a 20% change in the rightward shift in the treatment group compared with the control (power 80% with two-tailed test, significance 5%). An average of 110 infants less than 28 weeks gestational age are born per year at King Edward Memorial Hospital. All infants admitted in the neonatal intensive care unit will be screened daily to identify eligible infants. We expect to complete the recruitment in less than 3 years.

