### Statistical analysis

The data will be analysed statistically based on “intention to treat” using a statistical package (SPSS, version 24.0, IBM Corporation and others, USA). The primary outcome of right shift in the SpO_2_-PiO_2_ curve is a continuous outcome and will be reported as mean ± standard deviation for the intervention and control study groups. The primary outcome will be compared between the two groups using Student’s t test and the result will be reported as “mean difference with 95 % confidence intervals”.

Secondary outcomes will be compared between the two groups using χ^2^ test for categorical data and either the Mann-Whitney U test (not normally distributed) or Student’s t test (normally distributed) for continuous data. The correlation between serum and salivary vitamin A levels, and blood and saliva RDR values will be tested using Pearson r correlation analysis. Bland-Altman analysis will be used to analyse agreement between two assays. A “p” value of <0.05 will be considered statistically significant.

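### As written, the suspected-sepsis rule scores an infant who dies before day 5 of antibiotics as free of suspected sepsis, and it does not exclude culture-positive episodes

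*Protocol article*

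**What the plan says.** The third group of secondary outcomes in the protocol article opens with "Other secondary outcomes measured at discharge or death: Death before discharge". Infants who die are therefore classified on every outcome in that group.

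Two adjacent items in the group concern sepsis:

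- "diagnosis of culture positive sepsis (blood or cerebrospinal fluid"), with no C-reactive protein or antibiotic-duration condition;
- "diagnosis of suspected sepsis (C-reactive protein >25 mg·L^−1^ and treatment with antibiotics for at least 5 days"), with no culture condition and nothing on death during the antibiotic course.

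Under Statistical analysis, "Secondary outcomes will be compared between the two groups using χ^2^ test for categorical data". Each sepsis outcome is thus a yes/no count per infant, compared between arms. No other section of the article adds to either definition.

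**The concern.** The suspected-sepsis item is a complete operational rule: two criteria, both required. It goes wrong for two kinds of infant.

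The first is the infant who dies early. A minimum treatment duration can be met only by an infant who lives that long. Because the outcome is settled at discharge or death, a fatal episode shorter than 5 days is recorded as a *no* rather than as missing. In infants born before 28 weeks this is foreseeable. The error also has a direction: each such death lowers the suspected-sepsis count in its own arm, so an arm with more early septic deaths looks better on this outcome.

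The second is the infant with a positive culture. Listing the two outcomes side by side suggests that suspected sepsis means sepsis without a positive culture, but the criteria do not say so. If they are applied literally, some infants count under both headings. A chance imbalance in culture-positive sepsis can then carry into both comparisons, and a difference in suspected sepsis cannot be read as a difference in culture-negative disease. Two people abstracting the same record could also disagree, one coding by the outcome's name and the other by its criteria.

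**Working it through.** The article gives no sepsis rate and no planning figure for this outcome, so there is nothing to reproduce. The check is to apply the rule and then see what can be said about size.

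**Rule:** suspected sepsis = (C-reactive protein >25 mg/L) AND (antibiotic days ≥5).

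**Applied to four hypothetical records, one episode each:**

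| Record | Culture | C-reactive protein (mg/L) | Antibiotic days | Suspected sepsis | Culture-positive sepsis |
|---|---|---|---|---|---|
| A | negative | 60 | 5 | yes | no |
| B | negative | 60 | 3, then dies | **no** | no |
| C | positive | 60 | 10 | **yes** | yes |
| D | positive | 15 | 10 | no | yes |

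A is classified as the name implies. B is the fatal episode that neither sepsis outcome counts. C is counted in both. D shows the limit of the overlap: only culture-positive infants who also meet both criteria are added.

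**Size of the death effect.** The planned size under Sample size is 94 per arm. If all 94 are classified, one unscored infant lowers that arm's rate by 1/94 = 1.1 percentage points. If k₁ and k₂ infants are unscored in the two arms, the between-arm difference shifts by (k₁ − k₂)/94, so the comparison is biased only to the extent that the arms differ. The article gives neither number. Purely as an assumption, 1–3% of 188 infants would be 1.9 to 5.6, or about 2 to 6 infants over both arms.

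**Size of the overlap.** Let s be the proportion with culture-negative episodes, c the proportion with culture-positive sepsis, and q the share of the latter who meet both criteria. Ignore early deaths and infants with both kinds of episode. Then

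- literal rate = s + c·q
- culture-positive share of literal cases = c·q / (s + c·q)

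All inputs below are assumptions:

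| s | c | q | c·q | Literal rate | Culture-positive share |
|---|---|---|---|---|---|
| 0.20 | 0.15 | 0.6 | 0.09 | 0.29 | 0.09/0.29 = 31% |
| 0.10 | 0.15 | 0.6 | 0.09 | 0.19 | 0.09/0.19 = 47% |
| 0.20 | 0.30 | 0.9 | 0.27 | 0.47 | 0.27/0.47 = 57% |
| 0.10 | 0.30 | 0.9 | 0.27 | 0.37 | 0.27/0.37 = 73% |

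The table shows only that the overlap could be anything from a minority to a clear majority of the count, depending on rates that the article does not give.

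**The case against.** The best defence is that *suspected*, next to *culture positive*, already means not culture-proven, so the bracket only adds thresholds to a term that excludes positive cultures. Most analysts would probably code it that way. This stands in large part and makes the overlap the weaker half of the point. It does not help with early deaths, because no reading of *suspected* lets an infant who dies on day 3 complete 5 days.

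A second defence is that a condensed article may leave the ranking of episodes and the handling of interrupted courses to a fuller document. That would answer a complaint about missing detail. Here the article publishes an explicit rule, and the rule gives a definite wrong answer for a foreseeable infant.

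Third, a minimum duration sensibly separates treated sepsis from short rule-out courses. That is a good reason for the 5 days, but a course ended by death is not a rule-out course.

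A reader might also infer more than the article supports:

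- *That the two sepsis outcomes largely repeat each other, or that the rate is inflated by a known factor.* In two of the four assumed scenarios culture-positive infants are a minority of the count, and every input is assumed.
- *That early septic deaths vanish from the report.* They still appear under death before discharge, the first item in the same group. An infant with an earlier qualifying episode is still counted as well.
- *That the sample-size section bounds the number of deaths.* It says that "up to 20% of the recruited infants may not have SpO_2_-PiO_2_ measurement done at 36 weeks due to death", withdrawal or transfer. That is a pooled planning estimate: 0.20 × 188 is about 38 infants lost for all reasons, and it sets no limit on deaths.

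**Conclusion.** The point holds as a flaw in one secondary outcome. Taken literally, the rule cannot be met by an infant who dies during the antibiotic course before day 5, unless an earlier episode qualified. Each such infant is scored as having no suspected sepsis. That follows from the text alone. Bias in the comparison further requires the arms to differ in such deaths, which is not known.

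The overlap with culture-positive sepsis is also real on the literal wording, but it is partial and depends on the rule being applied without regard to its name. That culture-negative episodes were intended is an inference from the separate listing.

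Neither effect can be sized from the article. It would go too far to say that the outcome fails to measure suspected sepsis altogether, since it still captures culture-negative infants who receive at least 5 days of antibiotics. The primary outcome and the sample size of 188 are unaffected. This is a low-priority correction, worth making because it is cheap.

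**What to change.** Before unblinding, reword the outcome along these lines: *suspected sepsis: an episode with no positive blood or cerebrospinal fluid culture, C-reactive protein >25 mg/L, and antibiotics for at least 5 days, or until death if death occurs earlier during a course given for that suspected sepsis.* This changes only how outcomes are classified, not how any infant is treated.

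The exclusion then works by episode. An infant with a culture-positive episode and a separate culture-negative one may properly appear under both outcomes.

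The cost is one sentence. Culture results, C-reactive protein, antibiotic duration and death are already needed for the listed outcomes; the only addition is to confirm that a course cut short by death was given for the suspected sepsis. There are two small downsides. The count will differ from the one the literal rule would give, and a few infants who die of another cause while on antibiotics may be counted. Tying the course to the suspected sepsis limits the second but does not remove it.
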